## Abstract

**Background:**

In most countries throughout the world the construction industry continues to account for a disturbingly high proportion of fatal and nonfatal injuries. Research has shown that large enterprises seem to be most actively working for a safe working environment when compared to small and medium-sized enterprises. Also, statistics from Canada, Italy and South Korea suggest that the risk of injury among construction workers decreases with enterprise size, that is the smaller the enterprise the greater the risk of injury. This trend, however, is neither confirmed by the official statistics from Eurostat valid for EU-15 + Norway nor by a separate Danish study - although these findings might have missed a trend due to severe underreporting. In addition, none of the above mentioned studies controlled for the occupational distribution within the enterprises. A part of the declining injury rates observed in Canada, Italy and South Korea therefore might be explained by an increasing proportion of white-collar employees in large enterprises.

**Objective:**

To investigate the relation between enterprise size and injury rates in the Danish construction industry.

**Methods/Design:**

All male construction workers in Denmark aged 20-59 years will be followed yearly through national registers from 1999 to 2006 for first hospital treated injury (ICD-10: S00-T98) and linked to data about employment status, occupation and enterprise size. Enterprise size-classes are based on the Danish business pattern where micro (less than 5 employees), small (5-9 employees) and medium-sized (10-19 employees) enterprises will be compared to large enterprises (at least 20 employees). The analyses will be controlled for age (five-year age groups), calendar year (as categorical variable) and occupation. A multi-level Poisson regression will be used where the enterprises will be treated as the subjects while observations within the enterprises will be treated as correlated repeated measurements.

**Discussion:**

This follow-up study uses register data that include all people in the target population. Sampling bias and response bias are thereby eliminated. A disadvantage of the study is that only injuries requiring hospital treatment are covered.

## Background

Injuries related to construction work remain a serious problem worldwide. Although many prevention efforts and intervention programs have been undertaken [1,2], it is a known fact that construction workers continue to carry a particularly high risk of sustaining fatal and nonfatal injuries. The International Labour Organization (ILO) estimates that more than 100,000 construction workers around the world die every year - that is one person every five minutes [3]. In the European Union (EU-15 + Norway), workers employed in the construction sector from 1995 to 2005 showed the second highest incidence rate of fatal injuries at work and the highest incidence rate of nonfatal injuries at work [4]. Yet an overall trend of improvement is worth noting, as the total number of injuries in construction dropped 16% over the ten-year period. Still, the serious human and socio-economic consequences of approximately 1,000 European construction workers dying every year from work-related injuries and the 30,000 getting so severely disabled that they can no longer work, call for action [4(year 2005 figures)].

In EU's strategic plan for reducing the number of work-related injuries with 25% from 2007 to 2012, the construction sector is intelligibly stressed as particularly dangerous. Moreover, small and medium-sized enterprises (SMEs) - which according to EU are defined as enterprises with 10-49 and 50-249 employees, respectively - are considered to be especially vulnerable workplaces in terms of guaranteeing a healthy and safe working environment [5]. Several studies have underlined an elevated injury risk in SMEs [6-9]. One obvious reason for SMEs to be considered such risky and harmful workplaces is that they typically have fewer financial, human and technological resources available for organization and management of safety and health precautions. Economic survival and economic competition concerns quite often might override basic health and safety concerns. Another reason is that SMEs often seem to be lacking the ability to perform proactive or high-quality risk management [10-14]. In addition, the owner's reluctance towards state regulation of employees' health and safety issues seems to be decisive [15]. So in general large enterprises seem to most actively make an effort in ensuring a safe and sound working environment when compared to small and medium-sized enterprises.

The business pattern in the European Union is composed of 99% SMEs of which 92% are micro enterprises with less than 10 employees [16]. The investigation of construction SMEs, and especially micro enterprises, and their challenges to perform safety and health improvements thus continues to be of utmost importance for public health. Recent statistics from the European Commission from year 2005 show a higher injury incidence rate of around 6,500 per 100,000 construction workers in SMEs compared to an injury incidence rate of 4,700 per 100,000 construction workers in large enterprises. For fatalities in construction, the incidence rate is around 9 per 100,000 in SMEs while 5.5 for large enterprises [4].

The information obtained through comparisons of large enterprises (more than 250 employees) and SMEs (1 to 249 employees) is, however, not very useful in a Danish context. In Denmark the vast majority of enterprises, 92%, employ fewer than 10 workers, but only 2% employ more than 50 workers [17]. When looking at the Eurostat injury data for the relation between each enterprise size and not only SMEs against large enterprises in the construction industry, data do not indicate that injury rates increase with enterprise size among enterprises with less than 250 employees [4]. In fact, the reported injury rates among enterprises with 1-9 employees were lower than enterprises with 10-49 employees in each of the studied calendar years (1996-2005). EU's injury data, however, are subject to underreporting because data, in the case of Denmark, are based on injury reports to the National Labour Inspectorate exclusively lodged by employers.

Kines & Mikkelsen (2003) attempted to investigate rates of elevation fall injuries as a function of enterprise size in the Danish construction industry in the years 1993-1999 [18]. They used the following enterprise categorization: 0; 1-4; 5-9; 10-19; 20-49; 50-99; and > = 100 employees, yet their results were inconclusive; no noticeable trend was found. But as was noted by the authors, the investigation was possibly biased due to an underreporting of approximately 50% of the injuries. Moreover, enterprise size was not given in 13% of the reported injuries. Another problem with the study was that there was no control for the occupational distribution within the enterprises. According to Danish national data, injury rates among blue collar workers are on average twice as high as they are among white collar workers [19]. Also, it has been shown that injury rates differ between occupational categories among blue collar construction workers [20].

In contrast, three studies do indicate a trend of decreasing injury rates with enterprise size in the construction industry valid for the following settings: Ontario, Canada in the years 1988 to 1993 [21], South Korea in the years 1991 to 1994 [22], and Italy in the years 1995 to 2000 [8]. None of these three studies controlled for occupational distribution within the enterprises; hence, at least part of the decline in injury rates might be due to an increasing proportion of white-collar employees in the larger enterprises.

The primary aim of the present study is to investigate the relation between enterprise size and injury rates in the Danish construction industry, on a data set that is free from reporting bias, while controlling for the occupational distribution within the enterprises. A conditional aim will be to examine if there is an association between a change in Danish legislation and injury rates among construction workers in enterprises with 5-9 employees. The change, which was implemented from July 1, 2002, cancelled the requirement to have a safety organisation for enterprises with 5 - 9 employees and may have resulted in a higher risk of injury in these enterprises.

While performing the primary analysis, we will take the opportunity to estimate relative injury rates in the occupational groups that are included in the analysis. A special attention will be given to the rates among bricklayers, carpenters and plumbers whose work environment we plan to scrutinise in a subsequent project funded by the same grant as the present work.

## Methods/Design

The study is designed as an observational analytical population study. The population is dynamic (open for both entry and departure) and consists of all male construction workers in Denmark aged 20-59 years during the study period January 1, 1999 to December 31, 2006. The start of the study period coincides with the launching of the registration of all local workplace units in the Central Business Register in Denmark - a national register which contains primary data on all public and private businesses. The end of the study period refers to the year of the latest statistical returns on workplace size linked to local workplace unit from Statistics Denmark.

The subjects are followed one year at a time for first hospital treated injury during the year. The injuries are diagnosed on the basis of ICD-10 classification numbers S00-T98: "Injury, poisoning and certain other consequences of external causes" [23]. Included in the study are principal diagnoses as concluded either by discharge from the hospital, or by transfer to another hospital division.

### Data sources and classifications

The Danish Occupational Hospitalisation Register (OHR) is used to identify injured individuals. Included in the OHR are all persons who have been a legal/registered inhabitant of Denmark, aged 20 or more, at one time or another since 1980. OHR consists of a record-linkage between three national registers: 1) the central person register, 2) the national hospital patient register, and 3) the employment classification module.

The central person register contains information on gender, addresses, and dates of birth, death and migrations for everyone registered as living in Denmark sometime from 1968 to present.

The national hospital patient register contains data from all public hospitals in Denmark. Patient diagnoses have been coded according to the international classification of diseases version ten (ICD-10) since 1994. Since 1995, the register has covered all inpatients, outpatients, and emergency ward visits [24]. Relevant for the present study is that, in the follow-up period, no private emergency wards existed in Denmark, and that less than 1% of all planned surgery on in- and outpatients took place in private hospitals [25].

The employment classification module contains annually registered information on a person's industry, occupation, and employment status from 1975 onwards [24]. For the time-period spanned by the present study, the industries were initially coded according to the 1993 and then to the 2003 version of the Danish Industrial Classification of All Economic Activities [26,27]. These classification systems are national versions of the European Industrial Classification of All Economic Activities (NACE rev. 1). NACE rev.1 divides industries hierarchically into 17 level-1 sections identified by alphabetical letters A to U; 60 level-2 divisions identified by two-digit numerical codes (01 to 99); 222 level-3 groups identified by three-digit numerical codes (01.1 to 99.0), and 503 level-4 classes identified by four-digit numerical codes (01.11 to 99.00). In the present study only levels 1 and 2 are used; at level 1, the letter "F" refers to the construction industry and its level 2 number is "45".

The occupations in the employment classification module were coded according to DISCO-88 [28], which is a national version of the international standard classification of occupations (ISCO-88) [29]. DISCO-88 divides the occupations hierarchically into 10 major groups; 27 sub-major groups; 111 minor groups, and 372 unit groups. Included in the present study are the major groups related to manual construction work: group 7 "Craft and related trades workers"; group 8 "Plant and machinery operators and assemblers", and group 9 "Elementary occupations".

OHR-data of each injured individual will be linked to the latest national statistical returns of workplace size and local workplace unit. The statistical returns are assessed by Statistics Denmark every year in week 48, i.e. the last week in November, and imply that the employment data about each injured individual in the population stem from the year before the hospital treatment of the injury. Data about workplace size identifies the number of employees in addition to the owner of the workplace. Data about workplace unit identifies the local workplace unit where the injured individual was mainly carrying out his job. The local workplace unit can be the exact same as the mother enterprise unit, or it can be a unit belonging to the mother enterprise, but with a different geographical location and therefore with a different unit number. If a person worked in more than one place, which is often the case for construction workers, the local workplace unit is taken to be the workplace from where instructions emanate, or from where the work is organised.

Records are linked by means of a unique personal identification number and are kept at Statistics Denmark. Researchers are authorized to use data with encrypted personal identification numbers, and it is secured so that no analyses identifying any person or enterprise can be transferred outside Statistics Denmark.

### Study population

Inclusion criteria for the study population are:

• main employment in the construction industry (NACE code = '45');

• employment status as employee or self-employed, that is with the highest income as such during the year;

• job function as manual worker (DISCO-88 code = 7, 8 or 9);

• age from 20 to 59 years - the former time limit due to available OHR-data from the age of 20; the latter time limit due to the possibility of job release scheme from the age of 60;

• male worker - the women will be left out of the study since they constitute less than four percent of the blue-collar workers of the construction industry.

A person enters the population as soon as all of the above criteria are fulfilled, and departs whenever they are no longer met.

### Statistical analyses

A person will become a case once receiving a principal diagnosis in the ICD-10 interval S00-T98 ("injury, poisoning and certain other consequences of external causes") according to the OHR. For any given calendar year, a person will be censored at the time he becomes a case, emigrates or dies. Time-dependent dummy variables are used to categorise the manual workers into micro enterprises (fewer than 5 employees), small enterprises (5-9 employees), medium-sized enterprises (10-19 employees), and large enterprises (20 or more employees). A person's work category during a certain calendar year is determined by his enterprise association according to the population census performed in the end of November the preceding year.

The null hypothesis stating that "the injury rates among workers are independent of enterprise size" will be tested. If this first null hypothesis is rejected meaning that the observed injury rates most likely depend on enterprise size, a second null hypothesis will be tested. This second null hypothesis will test if "the relative rate of injury among workers in enterprises with 5-9 employees compared with other workers is independent of time period (January 1, 1999 - June 30, 2002 versus July 1, 2002 - December 31, 2005)". By this, it shall be tested if it can be assumed that the legislative change that took place in Denmark on 1 July, 2002, which cancelled the requirement of having a safety organisation in enterprises with 5 - 9 employees, did not have any effect on the injury rates among the workers in enterprises with 5-9 employees.

To deal with intra-enterprise correlations, a multi-level Poisson regression will be used to model the outcome, where the enterprises will be treated as the subjects while observations within the enterprises will be treated as correlated repeated measurements.

The analyses will be controlled for age (five-year age groups), calendar year (as categorical variable) and occupation. Occupation unit groups are: Bricklayers and stonemasons (DISCO-88 = 7122); Carpenters and joiners (DISCO-88 = 7124); Plumbers and pipe fitters (DISCO-88 = 7136); Electricians (DISCO-88 = 7137); Painters and wall-paper workers (DISCO-88 = 7141); Unskilled manual workers in construction workers (DISCO-88 = 9313).

The analyses will be performed by use of the GENMOD procedure in SAS version 9.1. Only main effects will be considered. The empiric standard error estimates will be used and an exchangeable correlation structure is assumed. The significance level will be set to 0.05. Table 1 shows the rate ratios and 95% confidence intervals that will be calculated.

**Table 1 T1:** Manual construction workers' relative risk rates of injury, by enterprise size and type of profession

	Injury Rate Ratio	Confidence Interval (95% CI)

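### The before/after test of the July 2002 law assumes that the 5-9 employee rate ratio had no trend of its own, and the plan includes no check of that assumption

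*Protocol article*

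**What the plan says.** The Background words a conditional aim as follows: "examine if there is an association between a change in Danish legislation and injury rates among construction workers in enterprises with 5-9 employees". That law took effect on 1 July 2002 and "cancelled the requirement to have a safety organisation for enterprises with 5 - 9 employees". The Background adds that this may have raised the risk of injury in those enterprises.

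The Statistical analyses section turns the aim into H2, tested only if the first null hypothesis (no relation between enterprise size and injury rate) is rejected. H2 states that the relative injury rate in the 5-9 class "compared with other workers is independent of time period", the periods being "January 1, 1999 - June 30, 2002 versus July 1, 2002 - December 31, 2005". The same paragraph says what the test is for: whether it can be assumed that the law "did not have any effect on the injury rates among the workers in enterprises with 5-9 employees".

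On time, the section says: "The analyses will be controlled for age (five-year age groups), calendar year (as categorical variable) and occupation". It then restricts the models to main effects. The Discussion treats selection into enterprises and misclassification of enterprise association. It does not mention time trends that differ between size classes.

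**The concern.** H2 compares one ratio of rates in two periods and uses the result to judge a law. For that use, two things must hold: without the law the 5-9 versus other ratio would have been the same in both periods, and the classes pooled as other workers (under 5, 10-19, 20 or more) follow one time course. The plan examines neither, although it holds seven years of dated data around a dated change.

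Adjusting for "calendar year (as categorical variable) and occupation" does not help. A calendar-year main effect removes movement common to all classes. Movement specific to the 5-9 class is exactly what the H2 term measures, so a slow drift and a step at July 2002 both load on the same coefficient.

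At stake is the policy reading. A significant H2 could reflect a trend that began before the law, and a null H2 could be a real effect offset by an opposite trend. The primary result on enterprise size is not affected.

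**Working it through.** The protocol gives no sample size, event count or power figure for H2, so there is no planned figure to reproduce. The steps below illustrate possible size.

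**1. Distance between the periods (from the protocol).** Before: 1999.0 to 2002.5, midpoint 2000.75. After: 2002.5 to 2006.0, midpoint 2004.25. Gap: 3.5 years.

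**2. H2 ratio under drift alone.** Let the log rate ratio of the 5-9 class change by d per year, with no law effect. The before/after ratio is exp(3.5 × d).

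| Assumed drift d per year | H2 ratio |
|---|---|
| 0.5% | exp(0.0175) = 1.018 |
| 1% | exp(0.035) = 1.036 |
| 2% | exp(0.07) = 1.073 |

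Masking works the same way. An assumed true law effect of 1.05 with drift of -1% per year gives 1.05 × exp(-0.035) = 1.014.

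**3. Chance of rejecting H2 under drift alone.** Assumptions: 10,000 to 80,000 events in total over both periods, 15% to 25% of them in the 5-9 class, two-sided 0.05, no overdispersion or clustering. With E_s and E_o the events per period in the 5-9 class and in the others, SE = sqrt(2/E_s + 2/E_o), and the rejection probability is P(|Z + 3.5d/SE| > 1.96).

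Worked case, 40,000 events and a 15% share: E_s = 3,000, E_o = 17,000, SE = sqrt(2/3,000 + 2/17,000) = 0.028. At d = 1%, 0.035/0.028 = 1.25, which gives 24%.

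| Total events | 1% drift | 2% drift |
|---|---|---|
| 10,000 | 10-12% | 24-33% |
| 40,000 | 24-33% | 71-86% |
| 80,000 | 42-57% | 94-99% |

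**4. Unequal trends among the comparators.** Suppose the 5-9 class is flat and only the micro class (assumed to be 30-50% of the comparator) falls by 2% per year. The H2 ratio is then 1.020 to 1.034 although nothing changed in the 5-9 class.

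**5. Cost of fitting a trend and a step together.** Over two equal periods of total length T, cov(time, step) = T/8, var(time) = T²/12 and var(step) = 1/4. So R² = (T²/64)/(T²/48) = 0.75, the variance inflation is 1/(1 - 0.75) = 4, and the SE of the step doubles. In the worked case an assumed law effect of 1.05 (log 0.0488) is detected with about 41% power by the planned contrast (SE 0.028) and about 14% with the trend added (SE 0.056).

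**6. What a pre-period trend test can show.** Over 3.5 years var(time) = 3.5²/12 = 1.021, and the slope SE is sqrt((1/E_s + 1/E_o)/1.021). The worked case gives sqrt(0.000392/1.021) = 0.0196, about 2% per year. Across the assumptions in step 3 it runs from 1.1% to 3.9% per year. A non-significant pre-trend therefore does not exclude drifts of the size in step 2.

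**The case against.** The strongest reply has four parts.

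- **The aim is modest.** The Background speaks of an association, and H2 is a conditional aim. That stands as to priority. It does not settle the matter, because the Statistical analyses section states the test as one of whether the law had an effect.
- **Supporting analyses may sit in a fuller plan.** An article need not list every display. But the article does fix the contrast, the comparator, the main-effects restriction and the interpretation, and those together create the gap.
- **The comparator may be handled already.** A reader might infer that a shifting mix of micro, medium and large enterprises among the other workers would by itself bias H2. The documents do not support that. Size enters as time-dependent dummy variables, and if these stay in the H2 model next to a 5-9-by-period term, differences in rate level between the comparator classes are adjusted. What remains is the assumption that those classes share one time course.
- **A trend-plus-step model is a poor gatekeeper.** This stands. It doubles the SE of the step, so making attribution to the law depend on significance there would often dismiss a real effect.

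Half-yearly ratios throughout would also be unwise. Size class is fixed from the preceding November, and the Discussion says later moves pull estimates toward unity. Attenuation may therefore grow within each year and produce a sawtooth unrelated to the law.

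**Conclusion.** The concern holds in a limited form. H2 as planned cannot separate a law effect from drift specific to the 5-9 class or from unequal trends among the comparator classes. No check is planned, yet the result is to be read as evidence about the law.

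A reader might go further and infer that any gradual drift will be credited to the law, or that H2 has a known inflated error rate. Neither follows. Small drift may go undetected (in the worked case 0.5% per year is rejected about 10% of the time), and opposite drift would conceal an effect rather than create one. The documents contain no evidence that drift occurred. The ratios 1.036 and 1.073 depend only on the period dates and the assumed drift. The rejection percentages depend also on assumed event counts, class shares and independence, and should be read as illustration.

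This is a cheap improvement to a conditional aim, not a flaw in the primary analysis.

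**What to change.** 1. Keep the planned H2 contrast. State that the model contains all four size classes (three dummies) plus a 5-9-by-period term, and exempt that term from the main-effects restriction.
2. Prespecify a display of the 5-9 rate ratio with 95% CI by calendar year, with 2002 split at 1 July. Note beside it that misclassification may grow within a year, so the two parts of 2002 are not fully comparable with each other or with whole years.
3. Test the trend in the 5-9 ratio before July 2002. Report the slope with its CI, because the test alone has little power.
4. Repeat H2 against the under-5 and the 10-19 classes separately.
5. Report a model with a linear 5-9-by-time term plus a step at 1 July 2002 as a sensitivity analysis only. State that it roughly doubles the SE of the step, so loss of significance there is not evidence of no effect.
6. Word the conclusion as an association unless the pre-period ratios are compatible with no trend.

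All of this uses data already held. The cost is some extra analysis and a less definite conclusion about the law.

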The Occupational Hospitalisation Register is free of reporting bias. All hospital contacts are registered, and there are virtually no missing principal diagnoses. This can be contrasted with two alternative national data sources held by the Danish Working Environment Authority and the National Board of Industrial Injuries, respectively, to whom merely 45% of all work-related injuries are reported [30]. Another advantage of the study is that we have identification numbers on the people as well as the enterprises, which enables us to take intra-enterprise correlations into account. Since the local workplace unit number is based on each geographically bounded production unit, this study provides more precise information about workplace size than the mother company number which merely sums up the number of employed for all subordinated workplaces. The study is further strengthened by its sample size, which will afford sufficient statistical power to the various hypothesis tests.

A disadvantage of the Occupational Hospitalisation Register is that it leaves out injuries that do not need hospital treatment. Another disadvantage is that we have annual but not daily information about occupation and enterprise. Enterprise association at the time of the injury might be different from the enterprise association in the end of November the preceding calendar year and the occupational category might change during the course of the year. We believe that most of the occupational categories are quite stable since we are dealing with skilled workers. It would, for example, be unlikely that a trained carpenter would shift into a brick layer trainee in the course of a calendar year. The construction industry is, however, known for its high turnover rate [31]. Within a calendar year, a worker in a small enterprise might, for example, move to a large enterprise, where he is injured. According to our model, such an injury would erroneously be classified as having happened in a small enterprise. The size of an enterprise may also change during a calendar year. All such changes would bias our estimates toward unity; from this perspective, the estimates should be regarded as conservative. As such, we hope that our study will contribute to a better assessment of relative injury rates in small and medium-sized enterprises.

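### The test on the 2002 law is a test of no change, yet the plan uses it to decide whether no effect can be assumed, lists no estimate for it, and confines the model to main effects

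*Protocol article*

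**What the plan says.** The Statistical analyses section sets out two hypotheses in order. The first is that injury rates do not depend on enterprise size. The second (H2 below) is reached only on a condition: "If this first null hypothesis is rejected". H2 states that "the relative rate of injury among workers in enterprises with 5-9 employees compared with other workers is independent of time period", the periods being 1 January 1999 to 30 June 2002 and 1 July 2002 to 31 December 2005.

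The section then gives its only rule for interpreting H2: "it shall be tested if it can be assumed that the legislative change that took place in Denmark on 1 July, 2002", by which enterprises of this size no longer needed a safety organisation, "did not have any effect on the injury rates among the workers in enterprises with 5-9 employees".

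On the analysis itself, "The significance level will be set to 0.05", the model is confined to main effects, and "Table 1 shows the rate ratios and 95% confidence intervals that will be calculated". Table 1 has three enterprise-size rows and six occupation rows. It has none for period or for size by period.

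The Background calls the legislation question a conditional aim and names a higher injury risk as the possible consequence. The Discussion says of workers changing enterprise, and of enterprises changing size, during the year: "All such changes would bias our estimates toward unity".

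**The concern.** H2 is a point null of no change. Rejecting it is evidence of a change. Not rejecting it means only that the data are compatible with no change, and they may be equally compatible with an increase that matters. The plan nevertheless makes absence of effect the thing to be assumed, with no margin and no confidence-interval criterion to support it.

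Two further features make this harder to put right at the reporting stage. No H2 estimate is among those listed, so a reader could not see which increases the data exclude. And a model with main effects only has no term that carries H2.

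The direction of the error matters. The concern named in the Background is harm after a safety requirement was withdrawn, so the costly mistake is false reassurance. Bias towards unity is conservative when the claim is that a difference exists. When the claim is that there is no effect, it favours the claim.

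**Working it through.** **What the text settles.** Write RR1 for the 5–9 versus others rate ratio before 1 July 2002 and RR2 for the ratio after it. H2 is RR2/RR1 = 1. In a log-linear Poisson model, ln(RR2/RR1) is the coefficient of (5–9 versus others) × (after versus before). A model with only size, age, calendar year and occupation as main effects forces RR2 = RR1, so it assumes H2 and cannot test it. The model statement and H2 therefore cannot both stand as written.

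**How much a non-significant result could hide.** The article gives no worker numbers, event counts, effect size or power figure, so there is nothing to reproduce. The following is an illustration.

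Inputs from the protocol: significance level 0.05 (sidedness not stated; two-sided assumed) and 3.5 years per period, from the stated dates.

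Inputs assumed: N = 80,000–160,000 workers; 15–20% of them in the 5–9 class; 8–12% injured per year; design effect DE = 1.0–1.5 for clustering; either no dilution or 30% dilution of the log effect by lagged classification.

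Formulas, with a and b the events per period in the 5–9 class and in the others:

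- a = N × share × rate × 3.5; b = N × (1 − share) × rate × 3.5
- SE of the log ratio of rate ratios = √[DE × (2/a + 2/b)]
- 95% CI half-width at a null estimate = exp(1.96 × SE) − 1
- Power = 1 − Φ(1.96 − δ/SE), with δ = ln(1.05) = 0.0488 or ln(1.10) = 0.0953, multiplied by 0.7 under dilution

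| | Least favourable | Most favourable |
|---|---|---|
| N, share, rate, DE | 80,000, 15%, 8%, 1.5 | 160,000, 20%, 12%, 1.0 |
| a; b | 3,360; 19,040 | 13,440; 53,760 |
| SE | 0.0324 | 0.0136 |
| CI half-width | 6.6% | 2.7% |
| Power, 5% increase | 32% | 95% |
| Power, 5% increase, diluted | 18% | 71% |
| Power, 10% increase | 84% | >99% |
| Power, 10% increase, diluted | 54% | >99% |

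The protocol supplies the direction of the dilution for its size estimates. Carrying it over to H2 assumes similar misclassification in both periods, and the 30% is an assumption.

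**Does the first hypothesis contain the second?** No. Suppose the 5–9 ratio moves from 1/√1.10 = 0.953 to √1.10 = 1.049, so RR2/RR1 = 1.10. The average over the two periods is (0.953 + 1.049)/2 = 1.001. If no other size class differs, a 3-df test of size rejects about 5% of the time. With 15% of events in the 5–9 class and no clustering, H2 itself would have power 0.67 at 20,000 events and 0.97 at 50,000 (both counts assumed). The case is constructed. It shows only that a flat overall size effect says nothing about the law.

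**The case against.** The sentence on what can be assumed may be a loose restatement of the null. The Background words the aim neutrally, as examining an association, and nothing says that p > 0.05 will be published as proof of harmlessness. This has some force: false reassurance is a risk that the wording permits, not a stated intention. But the sentence is the only interpretation rule given for H2.

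Table 1 is titled by enterprise size and profession, so it may be a shell for the primary analysis, with the H2 table left to a fuller plan. A reader might infer that H2 will yield only a p-value. The article does not say so; it only fails to list the estimate. The main-effects restriction is different, because the article states it outright and it conflicts with H2.

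A reader might also take the conditional order ("If this first null hypothesis is rejected") to be an error. It is not. It is openly declared, and fixed-sequence testing is a legitimate way to control type I error. Nor do the documents show that the first hypothesis is likely to survive. It is a test of independence, not of trend. The Background reports size differences in the Eurostat data and three studies with rates falling as size increases, and it calls the earlier Danish result inconclusive and possibly biased by underreporting.

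Finally, a national register may have ample power. The Discussion claims sufficient power but gives no figures. If that is right, the interval will be narrow and costs nothing to report. If it is not, the interval is indispensable.

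**Conclusion.** The point holds for the inference and for the model. A non-significant H2 test cannot show that the law had no effect, the plan gives no margin or interval by which to judge that, and the stated model excludes the interaction that H2 requires. These conclusions rest on the text alone.

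The power figures are illustrative because every count behind them is assumed. They should not be turned into a probability that the study will wrongly declare no effect: the result depends heavily on the effect chosen, and a 10% increase would be missed far less often than a 5% one. What they support is modest. Even with tens of thousands of events, an increase of a few per cent could go undetected, more so if lagged classification dilutes it.

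The testing order needs no change. The matter affects a declared conditional aim and leaves the primary size comparison untouched.

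**What to change.** 1. Exempt H2 from the main-effects restriction. Add a (5–9 employees versus others) × (before/after 1 July 2002) term, together with a period main effect, because calendar year 2002 spans both periods.
2. Add a row to Table 1, or a short second table, for the ratio of rate ratios with its 95% confidence interval.
3. Replace the wording on assuming no effect. If the test is not significant, say that no change was shown and that increases above the upper confidence limit are excluded. Fix a margin before analysis only if a claim of no relevant effect is wanted; the limit must then lie below it.
4. Keep the order of the tests. If the first hypothesis is not rejected, report the H2 estimate and interval as descriptive, outside the hierarchy, so that the declared error control is unchanged.

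The cost is one model term with its period indicator, follow-up in 2002 split at 1 July, one table row and a few sentences. No new data are needed.
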